**The median number of SLNs collected:**

Summary statistics (mean, median, standard deviation, minimum, and maximum) of the number of SLNs will be displayed for each treatment group.

**The metastatic rate of SLNs:**

The metastatic rate of SLNs, defined as the number of patients who have at least one positive SLN divided by the number of patients whose SLNs were identified.

**Operative duration:**

The operative duration is defined as the time from skin incision to resection of the SLN specimens among patients with at least one SLN detected and summary statistics (mean, standard deviation, minimum, and maximum).

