**SYNOPSIS**

| **Study Title** | Ultrasound-assisted carbon nanoparticle suspension mapping versus dual-tracer-guided sentinel lymph node biopsy in patients with early breast cancer (UltraCars): a prospective, randomized, controlled, phase 3 trial |
| --- | --- |
| **Clinical Phase** | Phase III |
| **Centers in which trial will be carried out** | Guangdong Provincial People's Hospital, Guangdong Academy of Medical Sciences (Guangzhou, China). |
| **Clinical Research Ethics Committees which have approved the study** | This study was approved by the Research Ethics Committee (No. GDREC2019610H) |
| **Good Clinical Practice (GCP) Study Monitors** | [name]: [contact]  [name]: [contact]  [name]: [contact]  [name]: [contact] |
| **Objectives** | **Principal objective:**  To compare the identification rate of sentinel lymph nodes (SLNs) using an ultrasound-assisted carbon nanoparticle suspension mapping versus dual-tracer-guided sentinel lymph node biopsy in patients with early breast cancer, defined as the number of patients whose SLNs were detected divided by the total number of patients included.  **Secondary objectives:**   - Median number of SLNs collected; - The metastatic rate of SLNs, defined as the number of patients who have at least one positive SLN divided by the number of patients whose SLNs were identified; - Operative duration, defined as the time from skin incision to resection of the SLN specimens; - Intraoperative or postoperative complications.   **Exploratory objectives:**  The identification rate of SLNs in patients after neoadjuvant therapy. |
| **Study design** | This study is a single-centre, open-label, randomized controlled, non-inferiority, phase 3 trial. Patients will be randomly assigned (1:1) using a permuted block randomization scheme to receive either ultrasound-assisted CNS (UC group) or CNS plus ICG dual-tracer-guided (GC group) SLN mapping.   - UC group: Intraoperative ultrasound-assisted CNS will be used for SLN mapping. - GC group: CNS plus ICG dual-tracer-guided SLN mapping.   All removed lymph nodes will be sent for intraoperative frozen section analysis. Axillary lymph node dissection will be undertaken according to the pathologic findings of the SLNs and the current international guidelines. |

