**1.1.4 Ultrasound-guided Surgery**

ICG and RI are able to provide deep insight into the SLNB location prior to skin incision. However, when the CNS technique is used alone for SLNB, it depends on the surgeon's naked-eye observation and experience, which may prolong the duration of surgery. Therefore, locating black-stained lymph nodes during surgery still requires improvement.

An easily available and feasible method to improve the amount of healthy breast tissue spared while ensuring tumor-free resection margins is intraoperative ultrasonography (US). US-guided surgery enables the surgeon to visualize the tumor during excision. Previous studies have clearly shown the efficacy of US-guided surgery for nonpalpable tumors. Rahusen et al. reported that US-guided surgery, during which an experienced radiologist performed the US, is superior to wire-guided surgery with respect to tumor-free resection margins (89% and 55% of cases, respectively). Snider et al. also showed an excellent rate of tumor-free resection margins using USS (82%) with a smaller volume of healthy breast tissue resection compared to wire-guided surgery (62.2 cm^3^ and 81.1 cm^3^, respectively)^69-74^.

Previous anatomical studies have revealed that the SLNs are neither evenly nor randomly distributed in the axilla but are instead located in predetermined anatomical regions. K.B. Clough et al. found that the SLNs in 86.8% of breast cancer patients were located in the area adjacent to the lateral thoracic tributary of the axillary vein (LTV), extending from the lower border of the axilla to the second intercostobrachial nerve (ICBN), and, more noticeably, 98.2% of SLNs were found in the medial part of the axilla, alongside the LTV, regardless of the site of the primary tumors^75^. These results are consistent with a previous autopsy study in which 87% of axillary SLNs were located between the lateral border of the pectoralis major muscle and the thoracoepigastric vein^76^. Considering the close proximity between the LTV and the lateral border of the pectoralis major muscle^76-68^, the present study used the lateral border of the pectoralis major muscle as a convenient surface landmark for the localization of axillary SLNs.

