**2.2 Secondary Objectives**

- To compare the median number of SLNs collected;
- To compare the metastatic rate of SLNs, defined as the number of patients who have at least one positive SLN divided by the number of patients whose SLNs were identified;
- To compare the operative duration, defined as the time from skin incision to resection of the SLN specimens in patients with at least one SLN detected;
- To compare the intraoperative or postoperative complications.

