**Experimental arm (****UC group):**

One milliliter of CNSs will be subcutaneously injected into the areolar area in the upper outer quadrant of the breast. The injection site will be massaged for 15 minutes to promote drainage of the tracer into the axilla. During the intraoperative ultrasound-assisted procedure, an ultrasound diagnostic system will be used. Before making the incision, ultrasound-guided exploration of the SLNs will be performed by placing the probe on the lateral border of the breast and sliding it cranially along the lateral border of the pectoralis major muscle. A sterile skin marker will be used to mark the optimal site of incision over the targeted lymph nodes, and the distance from the skin to the nodes will be measured by ultrasound and recorded in millimeters. Blunt dissection is carried out to identify the CNS-stained nodes around the marked region. An ultrasonography probe is placed repeatedly in or around the wound at different angles for adequate visualization if the SLNs could not be localized with further dissection. All black-stained lymph nodes or suspicious lymph nodes will be excised.

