**Control arm (GC group):**

One milliliter of CNSs will be subcutaneously injected into the areolar area in the upper outer quadrant of the breast. The injection site will be massaged for 15 minutes to promote drainage of the tracer to the axilla. One milliliter of diluted ICG (2.5 mg/ml) will be subsequently injected into the areolar area in the upper outer quadrant of the breast. A fluorescence tracer system will be used to visualize the subcutaneous lymph vessels and localize the SLNs. All fluorescent or black-stained lymph nodes along with any suspicious nodes will be removed. The remaining surgical field will be reexamined to ensure complete resection of the fluorescent lymph nodes.

An SLN number will be collected immediately following excision of each lymph node:

- A sentinel lymph node is defined as any lymph node that is either “fluorescent” and “black”, “fluorescent” only, “black” only, or a palpable suspicious lymph node.
- A “fluorescent” SLN is defined as a node that emits fluorescence under near-infrared camera detection.
- A “black” SLN is defined as any lymph node that is visibly stained black, has a visible contiguous black-stained afferent lymphatic, or both.
- Digital palpation (for the detection of intraoperatively clinically grossly suspicious (i.e., enlarged or hard) lymph nodes) will also be conducted.

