**6.2 Study Populations**

The primary efficacy analysis will be carried out on the intent-to-treat population (ITT), which is defined as the population who underwent SLNB. The ITT analysis will be carried out for the identification rate, the median number of SLNs collected, the operative duration, and the intraoperative or postoperative complications.

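### Operative duration starts at skin incision, so it omits the UC arm's pre-incision ultrasound work and possibly some GC localization; the sections also disagree on who is analysed

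*Protocol*

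**What the plan says.** The clock is the same wherever the endpoint is defined; the population is not.

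- Synopsis, secondary objectives: "Operative duration, defined as the time from skin incision to resection of the SLN specimens", with no restriction to patients in whom a node was found.
- Section 2.2: "the time from skin incision to resection of the SLN specimens in patients with at least one SLN detected".
- Section 6.3.3, operative duration: "the time from skin incision to resection of the SLN specimens among patients with at least one SLN detected".
- Section 6.2: "The ITT analysis will be carried out for the identification rate, the median number of SLNs collected, the operative duration". The ITT set is defined there as those who underwent SLNB.

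The procedures in section 5.2 show what falls on each side of the incision.

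- UC arm, before the incision: "Before making the incision, ultrasound-guided exploration of the SLNs will be performed by placing the probe on the lateral border of the breast". The skin mark and the skin-to-node distance belong to the same pre-incision step.
- UC arm, after the incision: blunt dissection and, if nodes are not localized, "An ultrasonography probe is placed repeatedly in or around the wound at different angles for adequate visualization".
- GC arm: a further injection of ICG after the massage, then "A fluorescence tracer system will be used to visualize the subcutaneous lymph vessels and localize the SLNs". The text does not place the imaging before or after the incision, but section 1.1.4 says "ICG and RI are able to provide deep insight into the SLNB location prior to skin incision".

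Section 6.3.3 compares the arms by t-test at P<0.05. No section adds a pre-incision or total procedure time, or a stop time for a search that finds nothing.

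**The concern.** The arms differ in how the node is localized, and part of that work is done before the clock starts. The UC scan certainly is. GC imaging and the ICG injection may be. A difference in incision-to-resection time could then reflect where the work was placed and not how much there was. Section 1.1.4 raises longer surgery as a drawback of CNS used alone, so a shorter recorded time in the UC arm would probably be read as a benefit of ultrasound.

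The second issue is the analysis set. Finding a sentinel node happens after randomization and is the primary outcome, so restricting duration to those patients conditions a secondary comparison on it. The sections also conflict: section 6.2 names a wider set than sections 2.2 and 6.3.3 allow.

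**Working it through.** **1. What is timed.**

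| Step | UC | GC |
| --- | --- | --- |
| CNS injection and 15-minute massage | common to both arms | common to both arms |
| ICG injection | none | after the massage; timing against the incision not stated |
| Initial localization | before the incision, untimed | fluorescence imaging; timing against the incision not stated |
| Search and dissection in the wound | timed, including repeat probe use | timed |

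Let A be the mean untimed arm-specific work in UC and B the same in GC. The recorded difference then flatters UC by A − B minutes. The protocol gives neither. Purely as an assumed range, a UC scan of 2 to 10 min and GC pre-incision imaging of 0 to 5 min give A − B from 2 − 5 = −3 min to 10 − 0 = +10 min. Any ICG injection time before the incision would add to B. The sign is not fixed.

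**2. The plan's own sample size, as the basis for counting failed searches.** Section 6.3.5 assumes 96% in both arms, a 6-point margin, one-sided α of 0.05 and 80% power.

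n per arm = (1.645 + 0.842)² × 2 × 0.96 × 0.04 / 0.06² ≈ 132, so 264 in total. With 10% dropout, 264 / 0.90 = 293.3, rounded up to 294. Both figures match the protocol.

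**3. Patients removed by the restriction** (n × failure rate).

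| Identification rate | of 132 | of 147 |
| --- | --- | --- |
| 96% (planned) | 5.3 | 5.9 |
| 90% (UC at the margin) | 13.2 | 14.7 |
| 99% (the group's previous CNS study, section 1.1.3) | 1.3 | 1.5 |

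**4. Effect on mean duration.** If a failed search lasts d minutes longer than a successful one and a fraction q fail, the mean over all patients exceeds the mean over successes by q × d. Dropping failures lowers the arm mean by that amount. The protocol gives no d; 5 to 30 min is assumed.

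- q = 4%: 0.04 × 5 = 0.2 min to 0.04 × 30 = 1.2 min.
- q = 10%: 0.10 × 5 = 0.5 min to 0.10 × 30 = 3.0 min.
- Between arms, 4% in each and equal d: 0.
- Between arms, 4% in each, d of 30 in one arm and 5 in the other: 0.04 × 25 = 1.0 min.
- Between arms, UC at 90%, GC at 96%, equal d: (0.10 − 0.04) × d = 0.3 to 1.8 min in favour of UC.

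**5. Can the stated populations all hold?** The stop event is removal of the sentinel node specimens. A patient with no node found has no such event, so the synopsis wording already yields no value for her. Section 6.3.6 then drops anyone with a missing value. Section 6.2, read as all who underwent SLNB, cannot be carried out without an added end time.

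**The case against.** Incision-to-resection is a clear measure, defined in the same way for both arms. Most of the search (the dissection and any repeat probe use) is on the clock, so a reader who inferred that localization is mostly untimed would go beyond the text: only the initial scan, mark and depth measurement in UC are certain to be missed. This stands.

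A reader might also infer that the endpoint favours UC. The documents do not support a direction, because GC may have untimed steps too.

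Nor do they support saying that this clock defeats the endpoint's purpose. The drawback named in section 1.1.4 is naked-eye searching, which takes place after the incision and is timed. With no CNS-alone arm, no choice of clock could test whether ultrasound cures that drawback.

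On the analysis set, the restriction largely follows from the stop event, and few patients are affected. A distortion of a minute or more from dropping failures needs assumed search times together with a large imbalance in failures or in failed-search times. An imbalance in failures would itself show in the primary endpoint. The GC procedure also counts a palpable suspicious node as a sentinel node, so true failures may be rarer than 4%. All of this stands.

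What remains is that an arm-specific step lies outside the clock in a formally tested between-arm comparison, and that the stated populations conflict.

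**Conclusion.** The point holds as a limited one about a secondary endpoint. Operative duration as defined omits known UC localization work and possibly GC work, so a recorded difference cannot by itself be taken as a difference in total localization time. Direction and size cannot be derived from the protocol; the −3 to +10 min range rests wholly on assumed times.

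The restriction to patients with a node found removes about 5 to 6 per arm at the planned 96%. Its expected effect on the comparison is nil if failure rates and failed-search times are equal across arms, and 0.3 to 1.8 min only under the margin scenario with an assumed 5 to 30 extra minutes per failed search. The conflict between section 6.2 and sections 2.2 and 6.3.3 is a matter of text and needs no assumption. The primary non-inferiority result and the sample size are not touched.

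**What to change.** 1. Keep incision-to-resection time as defined.
2. Add total localization time in both arms, from the first arm-specific step after the massage (first probe placement in UC, ICG injection in GC) to resection of the last sentinel node. Starting GC at the injection, not at the first camera view, keeps its extra step on the clock.
3. Base any claim of a time advantage on the total time.
4. State one population in the synopsis and sections 2.2, 6.2 and 6.3.3. Either label duration as conditional on detection and report the number of failed searches per arm, or include all who underwent SLNB, with a recorded end-of-search time, as a sensitivity analysis.

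The cost is one or two extra time stamps on the operative worksheet and wording changes in four places, with no added patients or procedures. The drawback is that the end time of a failed search is somewhat subjective in an open-label trial, but it concerns only a handful of patients.

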**6.3.4 Safety Analyses**

The occurrence of any drug-related adverse events is not expected. The most likely drug-related adverse events include allergic reactions, local inflammatory reactions, and skin or fat necrosis.

An adverse event is any untoward, undesired, and/or unplanned clinical event in the form of signs, symptoms, disease, or laboratory testing, or physiological observations occurring in a human participating in a clinical study with a study drug, regardless of the causal relationship. This includes the following:

- Any clinically significant worsening of a preexisting condition.
- Any recurrence of a preexisting condition.
- An AE occurring from overdose of a study drug whether accidental or intentional.
- An AE occurring from abuse of a study drug.
- An AE that has been associated with the discontinuation of the use of a study drug.

A serious adverse event (SAE) is any AE occurring at any dose that results in one or more of the following outcomes:

- Death.
- Life-threatening situation.
- Inpatient hospitalization or prolongation of an existing hospitalization.
- Persistent or significant disability or incapacity.

**6.3.5 Determination of Sample Size**

The sample size for the study is based on the primary endpoints. The non-inferiority (one-sided) hypothesis is adopted, which assumed an SLN identification rate of 96% for each group^79^ and a non-inferiority margin (∆) of 6% to secure an identification rate above 90% (one-sided test significance level (α) =0.05). A sample size of 264 patients was required to give a power of 80% to reject the null hypothesis that the identification rate in the UC group is inferior to that of the GC group by more than a 6% non-inferiority margin (with a 5% probability of type I error). Anticipating a 10% dropout rate, at least 294 patients will need to be recruited.

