| **Study population and total number of patients** | PASS 2019 software was used to calculate the required sample size. The non-inferiority (one-sided) hypothesis is adopted, which assumed an SLN identification rate of 96% for each group, and a non-inferiority margin (∆) of 6% to secure an identification rate above 90% (one-sided test significance level (α) =0.05). A sample size of 264 patients was required to give a power of 80% to reject the null hypothesis that the identification rate in the UC group was inferior to that of the GC group by more than a 6% non-inferiority margin (with a 5% probability of type I error). Anticipating a 10% dropout rate, at least 294 patients will need to be recruited. |
| **Timing and planned completion date** | **Initiation of inclusion:** December 2019  **Completion of inclusion:** May 2021  **Final analysis:** Third quarter 2021 |

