**1.1.3 Carbon Nanoparticle Suspensions (CNS)**

Another promising sentinel lymph node tracer is carbon nanoparticle suspensions (CNS). With advancements in nanotechnology, CNS could be widely used in surgeries. CNS, which contains particles with a diameter of 150 nm, can easily pass through the lymphatic vessels (diameter, 120–500 nm) but are unable to pass through the blood capillaries (diameter, 20–50 nm). Previous studies have demonstrated the safety of CNS^64^. In recent years, CNS has been used as a lymph node tracer during surgeries for thyroid cancer, gastric cancer, and colorectal cancer^65-67^.

Our previous study showed that CNS is a nonallergic sentinel lymph node tracer that has a good detection rate (99%)^68^. CNS has a large particle diameter, so it has difficulty entering blood vessels. In addition, CNS can readily pass through the lymphatic vessels and ultimately accumulate in the lymph nodes, staining them black for easy recognition. The CNS dye stays in the lymph nodes for an extended time, giving the surgeon a sufficient window for SLN detection. Moreover, CNS does not cause black staining of the surgical area. However, surgeons do need a certain amount of time to practice and master this staining method for sentinel lymph node biopsy.

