**6.3 Statistical Methods**

The statistical analyses for the efficacy and demographic variables are described below. Unless otherwise stated, all hypothesis tests will be conducted using a two-sided α=0.1 (one-sided α=0.05) level of significance.

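### 264 patients cannot deliver both the 80% power and the 5% type I error claimed: the figure comes from a Wald approximation that is too liberal near 96%

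*Protocol*

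**What the plan says.** Protocol section 6.3.5 sets up a one-sided non-inferiority comparison of identification rates. It "assumed an SLN identification rate of 96% for each group" and uses a margin of 6 percentage points "to secure an identification rate above 90% (one-sided test significance level (α) =0.05"). It then states: "A sample size of 264 patients was required to give a power of 80% to reject the null hypothesis that the identification rate" (the null being that UC is worse than GC by more than the margin), "with a 5% probability of type I error". Allowing for 10% dropout, the recruitment target is at least 294. The synopsis repeats the claim: "A sample size of 264 patients was required to give a power of 80"%.

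Section 6.3 confirms the level: "all hypothesis tests will be conducted using a two-sided α=0.1 (one-sided α=0.05) level of significance". The synopsis names PASS 2019 as the software. Neither place names the test statistic or variance formula behind 264. Allocation is 1:1, so 264 means 132 per arm, and section 3 gives 147 per arm for 294.

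**The concern.** At an identification rate of 96%, each arm of 132 is expected to have 132 × 0.04 = 5.3 failures. A normal approximation that plugs the observed rates into the variance is unreliable with so few events: it tends to underestimate the standard error when an arm happens to have very few failures, and so rejects too often. If 264 comes from that approximation, its power and its type I error may not both be what the protocol says.

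In a non-inferiority trial a type I error means accepting a technique that is truly 6 points worse. If the test is liberal, that risk is understated. If a well-calibrated test is used, the chance of a positive result is below the figure on which the trial was sized. The choice of test can also decide a borderline result.

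**Working it through.** **Inputs (all from section 6.3.5 unless noted).** Rate 96% in each arm; margin 0.06; one-sided α = 0.05, so z = 1.645; power 80%, so z = 0.842; 1:1 allocation (Study Design); dropout 10%.

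**1. Reproducing 264 and 294.** Wald formula per arm:

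n = 2 × p(1 − p) × (z_α + z_β)² / Δ² = 2 × 0.96 × 0.04 × (1.645 + 0.842)² / 0.06² = 131.9, so 132 per arm and 264 in total.

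Dropout: 264 / 0.9 = 293.3, so 294.

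Other formulas do not give 264. The asymptotic score formula gives 162 per arm (324), and Wald at one-sided 0.025 gives 168 per arm (336).

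**2. Exact operating characteristics.** For every pair (UC successes, GC successes) from 0 to n, apply the test at nominal one-sided 5% and add up the binomial probabilities of the pairs that pass. Power is taken at 96% in both arms. Type I error is taken with UC exactly 6 points below GC.

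| Test | n per arm | Power | Type I error, GC 96% | GC 98% | GC 99% |
|---|---|---|---|---|---|
| Wald | 132 | 80.4% | 6.1% | 7.1% | 7.5% |
| Farrington-Manning score | 132 | 74.65% | 4.6% | 4.7% | 4.6% |
| Newcombe | 132 | 75.0% | 5.1% | 4.8% | 4.6% |
| Wald, continuity-corrected | 132 | 71.1% | 3.7% | 3.9% | 4.4% |
| Wald | 147 | 84.4% | 6.3% | 7.2% | 8.1% |
| Farrington-Manning score | 147 | 78.5% | 4.6% | 4.6% | 4.5% |

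**3. Is this only a matter of which test is chosen?** No. A test that holds 5% over the whole null must hold it at each null point. Take the point UC 91.6%, GC 97.6%. By the Neyman-Pearson lemma, the most powerful 5% test of that point against 96%/96% is the likelihood-ratio test, and its power bounds that of every valid test. The bound is:

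- 75.5% with 132 per arm;
- 79.6% with 147 per arm (all 294 evaluable).

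**4. Size needed for 80% power.** The score test first reaches 80% exact power at 152 per arm: 304 evaluable, and 304 / 0.9 = 337.8, so 338 recruited.

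**5. Results on which the tests disagree (132 per arm, critical value 1.645).**

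- UC 125/132, GC 127/132: difference −0.0152, Wald standard error 0.0256, z = (−0.0152 + 0.06) / 0.0256 = 1.75, which passes. The score statistic is 1.59, which fails.
- UC 128/132, GC 132/132: difference −0.0303, Wald standard error 0.0149, z = (−0.0303 + 0.06) / 0.0149 = 1.99, which passes. The score statistic is 1.44, which fails.

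**The case against.** **The arithmetic is right, and 5% is a nominal level.** 264 and 294 do follow from the stated inputs, and a reader may take 5% as the α entered in the software. That stands as a description of how the number arose. But the protocol presents 80% and 5% together as properties of the design, and no analysis has both.

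**The analysis test is not named and may be left to the SAP.** True, and the Wald origin of 264 is an inference, though a strong one. The absence of a named test is not the defect. The bound in step 3 covers any test that an SAP could specify.

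**The planned 95% interval would remove most of the inflation.** Section 6.3.2 plans a 95% interval. If it is two-sided and decides non-inferiority, the Wald type I error is 3.4% at GC 96% and 5.1% at GC 99%. But power then drops to about 71% (Wald) or 62% (score), further from 80%. The conflict between that interval and the one-sided 5% level is a separate matter that needs its own resolution.

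**The 99% rate is for CNS alone.** Section 1.1.3 reports it from the team's earlier study, not for the dual-tracer control. So 7.5% is an upper illustration, and 6.1% is the figure at the planning values. Equally, if both arms truly do better than planned, score-test power with 132 per arm recovers to 82.5% at 97%, 91.1% at 98% and 98.2% at 99%. This is a real mitigation, but the protocol's claim is made at 96%.

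**Dropout may be small.** The endpoint is observed at surgery, within 14 days of randomization. With all 294 evaluable, the score test has 78.5% power, only 1.5 points short.

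**Not every alternative holds 5% strictly.** Newcombe is at 5.1% at the planning boundary, so it is close to 5% rather than strictly below it. This does not affect the bound.

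**Conclusion.** The statement is wrong as written. At the planning values, 264 evaluable patients give either 80.4% power with a 6.1% type I error (Wald) or about 75% power with a type I error near 5% (score or Newcombe). The ceiling for any test that holds 5% across the null is 75.5%. The size is moderate: about 1 point of excess error at a 96% control rate and up to 2.5 points at 99%, or about 5 points of power, equivalent to 304 − 264 = 40 more evaluable patients.

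This rests on 1:1 allocation, independent binomial outcomes, the one-sided 5% rule applied as stated, and a true rate of 96% in both arms for power. It does not rest on the inference that PASS was run with the Wald option.

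**What to change.** 1. Name the Farrington-Manning score test, or a score interval at the matching level, as the primary non-inferiority analysis.
2. In section 6.3.5 and the synopsis, restate the design: 264 evaluable patients give about 75% power at one-sided 5% with 96% in each arm, and 78.5% if all 294 are evaluable.
3. If the Wald test is kept, replace the 5% claim with its actual type I error with 132 per arm: 6.1% at a control rate of 96%, up to 7.5% at 99%.

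The cost is wording in two places and one named method, and the stated power becomes less favourable. Enrolment need not change if that power is acceptable. If 80% is to be kept with the score test, the requirement is 304 evaluable patients (338 recruited), which is a decision for the sponsor. Naming the test before the data are seen also prevents a later choice between methods that disagree on borderline results.
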